
#### Phase 2

The goal of Phase 2 is to enroll approximately 140 patients across the three enrolling site EDs to establish current clinical practice patterns with regard to obtaining head CTs for patients who meet the study's inclusion/exclusion criteria. Prior to initiating patient enrollment, site principal investigators will brief emergency medicine and trauma faculty about the research study, the POC whole blood TBI test, and how to interpret the test results. The intent of this phase is to establish early stakeholder engagement and obtain feedback from frontline clinicians that will inform development of the implementation blueprint in Phase 4.

Timeline of participant outcome assessments can be viewed in Table 1. The primary endpoint of this phase is the rate of head CTs completed in enrolled patients. The secondary endpoint of this phase is the rate of head CTs completed in enrolled patients with negative POC whole blood test results. These primary and secondary endpoints were selected to match the FDA's framing of clinical benefit and to be directly comparable to ongoing and completed studies evaluating utility of blood biomarkers for CT utilization in the ED (6, 17–19). Additional secondary outcomes include ED length of stay (in minutes), return to ED for the same injury within 2 weeks of first ED presentation (yes/no), Military Acute Concussion Evaluation-2 (MACE-2) results, Neurobehavioral Symptom Inventory (NSI), and two customized surveys about knowledge of mTBI and knowledge of the effects of radiation exposure in healthcare settings. ED length of stay can be extracted from the electronic medical record by research personnel, as presentation and discharge from the ED are timestamped. The MACE-2 is a multimodal tool which assesses clinical signs of TBI, incident description, signs, symptoms, medical history, a brief cognitive exam, neurological exam, and modified Vestibular Ocular Motor Screening (VOMS). The MACE-2 takes approximately 15 min to complete. The NSI is a 22-item scale of TBI symptoms since the time of injury.

**Table 1 T1:** Timeline of patient participant outcome assessments.

Outcome	Enrollment	Two-week follow-up
Military Acute Concussion Evaluation—2	X	
Neurobehavioral Symptom Inventory	X	X
Traumatic brain injury knowledge	X	
Radiation exposure knowledge	X	
Quality of Life After Brain Injury Overall Scale		X
Follow-up care survey		X

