Patients will also receive a series of surveys to complete remotely approximately 2 weeks after the initial visit. Patients will complete the NSI, the Quality of Life After Brain Injury Overall Scale (QOLIBRI-OS), and a brief custom survey about follow-up clinical care. The QOLIBRI-OS is a 6-item tool evaluating how a participant's brain injury has impacted their health-related quality of life.

#### Phase 3

The goal of Phase 3 is to design and deploy site-specific implementation blueprints based on determinants of use identified in Phase 1 and stakeholder feedback and practice patterns from Phase 2. The i-PARIHS framework will be used to select implementation strategies that will address identified facilitators and barriers from the Mi-PARIHS assessment in Phase 1.

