### Statistical analysis

Normality will be assessed for all outcomes, and appropriate transformations will be made to ensure that statistical assumptions are met prior to conducting all analyses. Statistical significance for these evaluations will be set at *p* < 0.05, and Bonferroni corrections will be applied to all analyses for multiple comparisons.

#### Phase 1

For Phase 1, descriptive statistics will be calculated for POC whole blood TBI test results, including the rates of elevated vs. non-elevated values, rates of CT scans ordered, and rates of return ED visits for the same injury within 2 weeks in the first group of 140 ED patient participants. Whether or not the patient returned will be self-reported at the 2-week follow-up survey sent to the participants. ED length of stay (in minutes) will be compared between patients who only received the POC whole blood TBI test and those who received the POC whole blood TBI test and a head CT scan using an analysis of covariance model, including enrollment site as a covariate. This analysis will be conducted only for participants with a negative POC whole blood TBI test to control for clinical severity of the injury. An exploratory analysis using receiver operating characteristic area under the curve (AUC) will be conducted to differentiate patients who return to the ED for evaluation of the same injury within 2 weeks from those who do not, using whole blood GFAP and UCH-L1 as predictors. Approximately 5% of patients diagnosed with TBI and GCS scores of 13–15 in the ED return to the ED within 72 h of discharge for TBI evaluation (27). The expected event rate would yield seven returns to the ED for the Phase 2 cohort of *n* = 140, which is lower than the standard expectation of 10 events per predictor. Statistical significance for these evaluations will be set to *p* < 0.05.

#### Phase 2

For Phase 2, descriptive statistics for all determinant measures will be calculated. Items from the Mi-PARIHS will be plotted as originally described for visual inspection of the weakest domains. These statistics will be calculated by site and by stakeholder type to facilitate presentation to the CAB and to inform development of the implementation blueprint.

Phase 3 will not have a corresponding statistical analysis because it is entirely dedicated to the development of the site-specific blueprints.

#### Phase 4

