### Anticipated impact on clinical practice

Several deliverables will be generated from the completion of this study that can meaningfully impact the clinical practice of evaluating mTBI patients in the ED. The primary deliverable is the open-access publication of site-specific implementation blueprints for designed to increase use of the POC whole blood TBI test. This will allow other Level 1 trauma center EDs with similar patient throughput and demographics to study how the test was implemented, enabling them to tailor strategies to at their own institutional contexts. We will also provide the first known evidence of the clinical utility of the test in predicting return visits to the ED for the same injury within a 2-week period. This protocol will also deliver crucial data on how implementation of the test reduces length of time spent in the ED, which is an endpoint with significant potential to influence uptake from a practical standpoint. Our intent is to use the data generated from the completion of this work to conduct a hybrid type III effectiveness–implementation clinical trial, evaluating the efficacy of optimized interventions to improve clinical uptake of the POC whole blood TBI test in EDs of varying sizes.

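### ED return within 2 weeks is ascertained only by a remote self-report survey, and about seven expected events in the first 140 patients cannot support the promised evidence on predicting revisits

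*Protocol article*

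**What the plan says.** Methods, Phase 2, lists return to the ED for the same injury as a yes/no secondary outcome, with a 2-week window counted from first presentation. Statistical analysis, under the heading Phase 1 (the text there concerns the first 140 patients, who are enrolled in Phase 2), fixes the source: "Whether or not the patient returned will be self-reported at the 2-week follow-up survey sent to the participants". Methods, Phase 2, describes that follow-up: "Patients will also receive a series of surveys to complete remotely approximately 2 weeks after the initial visit". No other source for ED return is named. For ED length of stay, the same section says that it "can be extracted from the electronic medical record by research personnel".

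The planned use of the outcome is an exploratory ROC AUC with GFAP and UCH-L1 as predictors. The event projection starts from this rate: "Approximately 5% of patients diagnosed with TBI and GCS scores of 13–15 in the ED return to the ED within 72 h of discharge". It continues: "The expected event rate would yield seven returns to the ED for the Phase 2 cohort", and the article adds that this is below the usual 10 events per predictor. Statistical analysis, Phase 4 (Secondary outcome comparison) lists the exploratory AUC again and does not say whether the two cohorts are combined. The Discussion, under Anticipated impact on clinical practice, states: "We will also provide the first known evidence of the clinical utility of the test in predicting return visits to the ED".

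**The concern.** There are two weaknesses in the same outcome.

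- **Ascertainment.** A return to an enrolling ED leaves a record in a system that staff already consult, yet under the stated plan it counts only if the patient answers a remote survey. Returns among non-responders are lost. If the chance of answering differs between patients who return and those who do not, the observed revisit rate is wrong. If it also depends on the biomarkers, the AUC is wrong too.
- **Information.** Seven events are few for an AUC, and every unanswered survey from a returning patient removes about one seventh of them.

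What is at stake is the deliverable on predicting return visits, and the revisit rate itself. The CT-rate comparison does not depend on either.

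**Working it through.** **Inputs from the article:** 140 patients per cohort, a 5% return rate (72 h), two predictors and a benchmark of 10 events per predictor. **Assumptions of this review:** the AUC values and the survey response rates; the article gives neither.

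**1. The plan's own figure.** 140 × 0.05 = 7 events, which matches. The benchmark with two predictors is 2 × 10 = 20 events. At 5% that needs 20 / 0.05 = 400 patients. Equivalently, it needs a return rate of 20 / 140 = 14.3% in one cohort or 20 / 280 = 7.1% in both. Under a binomial(140, 0.05) the central 95% range of the event count is 2 to 12, with a 17% chance of fewer than 5.

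**2. Precision in one cohort.** Hanley-McNeil, with n1 events and n0 non-events:

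SE² = [A(1−A) + (n1−1)(Q1−A²) + (n0−1)(Q2−A²)] / (n1·n0), where Q1 = A/(2−A) and Q2 = 2A²/(1+A).

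For A = 0.70, Q1 = 0.5385, Q2 = 0.5765 and A² = 0.49. With 7 and 133:

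SE² = [0.21 + 6 × 0.0485 + 132 × 0.0865] / 931 ≈ 11.91 / 931 = 0.0128, so SE = 0.113.

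- Symmetric 95% interval: 0.70 ± 1.96 × 0.113 = 0.48 to 0.92.
- Logit scale: SE = 0.113 / 0.21 = 0.539; 0.847 ± 1.056 back-transforms to 0.45 to 0.87.

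| AUC | SE | Symmetric 95% interval | Logit 95% interval | Approx. power against 0.5 |
|---|---|---|---|---|
| 0.60 | 0.116 | 0.37–0.83 | 0.37–0.79 | 0.15 |
| 0.70 | 0.113 | 0.48–0.92 | 0.45–0.87 | 0.43 |
| 0.80 | 0.102 | 0.60–1.00 | 0.53–0.93 | 0.78 |

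With the symmetric interval, 0.5 is first excluded at an AUC of about 0.72.

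**3. Survey loss (assumed, unrelated to outcome).** A 20% loss leaves 7 × 0.8 = 5.6 events, and AUC 0.70 then has a logit interval of 0.42 to 0.88. A 30% loss leaves 7 × 0.7 = 4.9 events and 0.40 to 0.89.

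**4. Differential response (assumed).** Observed rate = 0.05r / (0.05r + 0.95s), with r the response among returners and s among non-returners.

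| r | s | Observed rate when the truth is 5% |
|---|---|---|
| 0.80 | 0.80 | 5.0% |
| 0.60 | 0.80 | 0.030 / 0.790 = 3.8% |
| 0.50 | 0.80 | 0.025 / 0.785 = 3.2% |
| 0.90 | 0.70 | 0.045 / 0.710 = 6.3% |

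The error can go either way, and is nil if response is unrelated to return.

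**5. Both cohorts combined.** 280 × 0.05 = 14 events and 266 non-events. At AUC 0.70, SE = 0.080, giving 0.54 to 0.86 (logit 0.53 to 0.83), with power against 0.5 of about 0.71. Comparing patients only within phase and averaging the two results costs almost nothing: 0.113 / √2 = 0.080. Fourteen events are still short of 20.

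**The case against.** The authors have said much of this themselves. The AUC is called exploratory in both places, and the shortfall against the benchmark is stated openly, so nothing is concealed. Self-report is also a defensible choice. It can capture visits to any hospital, which a site's own record cannot, and attribution to the same injury takes judgement rather than a timestamp. ED return drives neither the primary endpoint nor the sample size. All of that stands, and it keeps the point to a secondary, exploratory part of the study.

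Three stronger readings are tempting, and the article does not support them.

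- A reader might infer that the results will be biased by non-response. No response rate is given, and nothing shows that patients who return answer less often; step 4 shows both directions.
- A reader might infer that two separate seven-event analyses are fixed. The figure of seven is given for the first cohort only, and the Phase 4 text is silent on combining cohorts, which an unseen analysis plan may settle.
- A reader might infer that one cohort can never separate the AUC from 0.5. That is true at 0.70 and below. At 0.80 the interval excludes 0.5 on either scale.

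The seven events also come from a 72-hour rate, so the 2-week count is probably higher and the intervals above are probably on the wide side.

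What the objection does not remove: survey self-report is the only source the text fixes, the admitted shortfall is followed by no remedy, and the Discussion's promise carries none of the caution in the analysis section.

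**Conclusion.** The point holds as a matter of ascertainment and of a claim that outruns its analysis. Returns among survey non-responders are lost although a record source is already in use, which puts the revisit rate and the AUC at risk of bias of unknown direction. With about seven events in the first cohort, an AUC of 0.70 has a 95% interval of about 0.48 to 0.92 (logit 0.45 to 0.87), even with complete follow-up. That cannot bear the Discussion's promise. The size rests on the article's 5%, which is a 72-hour figure used for a 2-week endpoint, and on an assumed AUC of 0.70. A higher 2-week rate would help, but one cohort would need 14.3% to reach the 20 events implied by the article's own benchmark. The change should be made; it does not affect the primary comparison of CT rates.

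**What to change.** 1. **Outcome definition.** Define ED return as either a visit for the same injury at an enrolling health system within 14 days of first presentation, confirmed from the medical record, or a self-reported visit elsewhere in that window. Survey non-responders then still have a record-based outcome.
2. **Analysis.** Run the exploratory AUC on both cohorts combined, stratified by phase because the blueprint is introduced between them, and report 95% confidence intervals. State that about 14 events are expected and that this is still below the 20 implied by two predictors.
3. **Event projection.** Say that seven is a projection from a 72-hour rate and that the 2-week count may differ.
4. **Discussion.** Replace the promise about clinical utility for return visits with a statement that the study will give exploratory, hypothesis-generating data on that question.

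Cost: a short record review per patient at day 14, including a judgement on whether the visit was for the same injury, and some rewording. Visits to outside hospitals by patients who do not answer the survey will remain unseen, and this should be stated as a limitation.

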##### Primary and secondary endpoint comparison

A Fisher's exact test will be conducted to evaluate the difference in proportions of GCS 13–15 TBI patients between Phase 2-enrolled participants (*n* = 140) and Phase 4-enrolled participants (*n* = 140). Another Fisher's exact test will also compare the difference in proportions of GCS 13–15 TBI patients with a negative POC whole blood TBI test who still received a head CT scan between Phase 2 and Phase 4. Subanalyses will be conducted for each site, as well.

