### Preliminary work

In a preliminary study conducted at a Level 1 trauma center ED with 104 patients presenting with suspected mTBI (7), we found that the POC whole blood TBI test delivered results 2.5 h faster than a head CT scan (even when using the original plasma version of the test, which requires laboratory processing). As most EDs do not have a centrifuge, the use of plasma as the testing matrix requires transport of the sample to the central clinical laboratory for receipt, accessioning, centrifugation, and the delivery to the testing area. With the new POC whole blood TBI test, we anticipate additional time savings of 45 min due to not having to send the sample to the central laboratory. Emergency medicine physicians were surveyed about their decision to obtain head CT scans despite negative values for both biomarkers, indicating unfamiliarity with the POC whole blood TBI test, familiarity with the CT scan, and the perspective that the CT scans are more sensitive/specific. All patients received a head CT scan, regardless of the POC whole blood test result. Overall, nearly one in five patients could have avoided a head CT scan (due to a negative POC whole blood TBI test) in this sample (7).

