## Methods

Figure 1 illustrates the four phases of the study, including the goal, study population, and primary outcome measure. This study aims to enroll 280 patients with acute GCS scores of 13–15 across three sites (Phase 2 = 140, Phase 4 = 140). The three enrolling sites represent academic Level 1 trauma centers with accompanying EDs from three distinct geographical regions of the United States. Target enrollment for each site includes 47 acute ED patients in Phases 2 and 4.

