The goal of Phase 4 is to test the effect of the implementation blueprint on clinical practice patterns with regard to obtaining head CTs for patients who meet the study's inclusion/exclusion criteria across the three enrolling sites. Approximately 140 patients with presenting GCS scores between 13 and 15 will be enrolled across the three sites. The primary endpoint of Phase 4 (to be compared with the outcome of Phase 2) is the rate of head CTs completed in enrolled patients. The secondary endpoint of this phase is the rate of head CTs completed in enrolled patients with negative POC whole blood test results. We will also evaluate if the implementation blueprint has impacted baseline perceptions of facilitators and barriers and related implementation outcomes (i.e., adoption, appropriateness, acceptability, decisions, and feasibility) has shifted provider's perspectives on the test by having those who completed Phase 1 surveys (e.g., Mi-PARIHS) complete the surveys again.

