### Sample size

#### Power analysis

The primary endpoint of the overall study is to evaluate the effect of the implementation blueprint by comparing the proportion of patients receiving head CTs in the first patient cohort (enrolled in Phase 2) with the second patient cohort (enrolled in Phase 4). Given that 100% of patients in our pilot study received a head CT scan (regardless of POC whole blood test results), we expect the proportion of head CT scans to be high for Phase 2 enrollments. We hypothesize that a 20% reduction of head CT scans in Phase 4 would be possible after the implementation of the blueprint, representing a clinically meaningful reduction.

A power analysis was conducted using a two-tailed Fisher's exact test for two independent groups, using the proportions of 95% for Phase 2 and 75% for Phase 4, an alpha of 0.01, and power of 0.99. The analysis yielded a sample size of *n* = 140 in Phase 2 and *n* = 140 in Phase 4, with a total of 280 participants with mild TBI. G*Power (version 3.1.9.6) was used for the power analysis.

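### Fisher's exact test is valid but conservative for the test-negative CT endpoint and the site sub-analyses; Boschloo's exact test would add modest power at no cost

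*Protocol article*

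**What the plan says.** The Phase 4 analysis section compares the Phase 2 and Phase 4 cohorts (140 each) on head CT with Fisher's exact test. For patients with a negative blood test it continues: "Another Fisher's exact test will also compare the difference in proportions". It then adds: "Subanalyses will be conducted for each site, as well". No test is named for those sub-analyses, so Fisher's test is implied by context only.

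The test-negative rate is a named endpoint: "The secondary endpoint of this phase is the rate of head CTs completed in enrolled patients with negative POC whole blood test results".

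The Power analysis section sizes only the overall comparison: "A power analysis was conducted using a two-tailed Fisher's exact test for two independent groups". Its assumed CT rates are 95% in Phase 2 versus 75% in Phase 4, with a 0.01 alpha and 99% power. The article gives no expected number of test-negative patients, no Phase 4 CT rate for them, and no power for this endpoint or for the sites.

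Two statements bear on the sizes. In the pilot, "nearly one in five patients could have avoided a head CT scan" because their blood test was negative. For the sites: "Target enrollment for each site includes 47 acute ED patients in Phases 2 and 4". The Statistical analysis section sets a 5% significance level and applies Bonferroni corrections for multiple comparisons.

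**The concern.** Fisher's test conditions on the total number of scans, which a comparison of two cohorts does not fix. In small groups with CT rates close to 100%, few tables are possible given that total, so the test can reject far less often than its nominal level allows. The high power of the overall comparison does not carry over to comparisons of about 27 or 47 per phase.

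The test-negative CT rate is the endpoint closest to the cleared rule-out use of the test. The blueprints are site-specific, so the site comparisons are the direct look at each one. In both, a real fall may be called non-significant when an exact test with the same error guarantee would detect it.

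**Working it through.** **Inputs.**
- Overall: 140 per phase, 95% versus 75%, two-sided alpha 0.01 (Power analysis).
- Test-negative patients per phase: 140 × 0.19 = 26.6, about 27. The 0.19 is an assumption, read from the pilot's statement; the article does not give this count.
- Site: 47 per phase (Methods).
- CT rates for test-negative patients and within sites: not given. The overall 95% to 75% is carried over as an assumption, and other falls are tried.

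**The plan's own figure.** Exact power of two-sided Fisher at 140 per phase, 95% versus 75%, alpha 0.01, is 0.9876. This rounds to the stated 0.99, so the sample size reproduces.

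**Method for the smaller comparisons.** All 2×2 tables are enumerated as two independent binomials. Power = Σ Bin(x₁; n₁, p₁) × Bin(x₂; n₂, p₂) over the tables that the test rejects. Size is the same sum with p₁ = p₂ = p, maximised over p. Boschloo's test uses the Fisher p-value as its statistic, with the largest cutoff whose maximum size is at most alpha. It therefore rejects whenever Fisher does.

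**Size at nominal 5%.**
- 27 per phase: Fisher's maximum is 2.6%. At a common CT rate of 95%, 90%, 85% and 80% it is 0.1%, 0.7%, 1.4% and 1.9%. Boschloo's maximum is 4.5%.
- Slightly unequal groups (27/26, 26/28, 28/26, 27/25): Fisher's maximum is 3.6% to 3.9%.
- 47 per phase: Fisher's maximum is 3.1% (3.96% at 46/47). Boschloo's is 4.95%.

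**Power at an unadjusted 5%** (sizes are Phase 2/Phase 4).

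| Comparison | Sizes | CT rates | Fisher | Boschloo | Gain (points) |
|---|---|---|---|---|---|
| Test-negative | 27/27 | 95% to 75% | 36.1% | 50.0% | 13.9 |
| Test-negative | 26/28 | 95% to 75% | 40.5% | 50.8% | 10.3 |
| Test-negative | 28/26 | 95% to 75% | 54.1% | 55.2% | 1.0 |
| Test-negative | 27/25 | 95% to 75% | 53.1% | 53.2% | 0.1 |
| Test-negative | 27/27 | 95% to 60% | 84.0% | 90.6% | 6.6 |
| Test-negative | 27/27 | 95% to 50% | 96.5% | 98.3% | 1.8 |
| Site | 47/47 | 95% to 75% | 70.8% | 79.3% | 8.4 |
| Site | 46/47 | 95% to 75% | 71.6% | 76.6% | 5.1 |
| Site | 47/46 | 95% to 75% | 77.5% | 81.6% | 4.2 |

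Gains come from unrounded powers.

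**Averaging over subset size.** The number of negatives is random. With both sizes drawn from Binomial(140, 0.19), the average gain is about 5 to 6 points at 95% to 75% (roughly 45% to 51%), about 2 to 3 at 95% to 60%, and under 1 at 95% to 50%. Starting from the pilot's 100% CT rate and falling to 80%, it is about 8 to 9.

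**Single tables.** For 26/27 versus 20/27, p = 0.0504 with Fisher and 0.026 with Boschloo. For 45/47 versus 38/47, p = 0.0502 and 0.031.

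**Adjusted levels, 95% to 75%.** At alpha 0.025 the gain is 2.8 points (27/27) and 6.3 (47/47). At 0.05/3 = 0.0167 and 47/47, power is 57.8% versus 61.0%, a gain of 3.2.

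**The case against.** Fisher's test is valid, prespecified and the one used for sizing. Nothing in the analysis section is wrong or contradictory; another valid test merely has more power in secondary analyses. That stands, and it keeps this minor.

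A reader might infer that the plan throws away 14 points of power. The documents do not support that as a headline. It needs exactly 27 versus 27, an unadjusted 5% level, and the overall CT rates carried into the test-negative subset. The article states none of these for that subset.

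The protocol's own hypothesis also points to a larger fall among negatives. A 20-point fall in 140 patients is 0.20 × 140 = 28 scans, about the whole test-negative group. If the 113 others stay at 95% and no negative is scanned, the overall rate is 113 × 0.95 / 140 = 76.7%. A 95% to 75% fall among negatives alone is only 27 × 0.20 = 5.4 scans, or 5.4/140 = 3.9 points overall. If the planned effect comes mainly from test-negative patients, Fisher's power is close to 100% and nothing is lost.

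This limits the gain but does not remove it. The Current work section lists entrenched barriers to use, so partial uptake is plausible, and that is where the choice of test matters. Bonferroni levels change the gain, and Boschloo's test cannot do worse at any level.

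Finally, Fisher's test for the site sub-analyses is inferred, and a fuller plan may fix another test. The site part is therefore conditional.

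**Conclusion.** The point holds as a minor inefficiency. Fisher's test is conservative for the test-negative endpoint and, if it is also used there, for the site sub-analyses. At an assumed 95% to 75% fall and an unadjusted 5%, Boschloo's test adds about 5 to 6 points on average for the test-negative endpoint, ranging from near 0 to 14 with the realised group sizes, and about 4 to 8 points per site. The gain nearly vanishes for large falls and varies with the Bonferroni level.

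These sizes rest on a negative fraction of about 0.19 and on CT rates that the article does not give for these subsets. A reader might also infer that the error rate is not controlled or that the primary result is at risk. Neither follows: Fisher's size stays below 5% throughout, and the primary comparison keeps 98.8% power at alpha 0.01.

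**What to change.** In the Phase 4 analysis section, name Boschloo's exact test for the test-negative endpoint and for the site sub-analyses, at the same two-sided, multiplicity-adjusted alpha. Report each difference in CT proportion with a matching unconditional confidence interval. The primary comparison can stay as planned. The cost is one sentence, written before outcome data are seen. Standard software provides the test, and no extra patients or data are needed.
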